### Primary outcome

The primary outcome is a composite endpoint of first non-elective hospital admission or death during the observation period measured as a binary outcome. This avoids issues of a potential trade-off between these two forms of event and also allows all patients to be included in the primary analysis. Primary outcome measures are recorded by the GPs when they occur or at follow-up visits every 8 months.

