### Blinding

Inherent to the study protocol GPs and patients cannot be blinded. The analyst will be kept blind to GP practice allocation.

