### Monitoring

Monitoring is performed according to a prespecified monitoring charter. Independent monitors selected by the corresponding study centers will conduct all monitoring. Inclusion and exclusion criteria will be checked electronically. The monitors will control whether the informed consent forms of all participants are correctly filled out and signed. All other data will be monitored at each follow-up visit in a random sample of 10 % of the GPs. On-site visits are performed at T0 and T3. Monitors will compare the entries of all study patient records to the entries in the eCRF regarding age, sex and medication. In a random sample of three patients, monitors will check the eCRF entries of the medication plus doses, diagnoses, falls, and laboratory results as well as height and weight, and compare these data to the patient record. Additionally at T3, monitors will check all reported and not reported non-elective hospital admissions as well as adherence to protocol visits with the practice record. At T1 and T2 monitors will check this via phone verification. Furthermore, at T1 to T3, monitors will monitor 100 % of the reported dropouts via phone verification, and in a random sample of 10 % of the practices they will check the reported hospital admissions and deaths of all patients of the practice.

For safety purposes, the PRIMA-eDS consortium will appoint a Safety and Data Monitoring Committee (SDMC) consisting of three experienced researchers, including one clinical trial statistician. The committee is independent from the investigators and will review the accumulated trial data. They will perform interim analyses regarding the primary endpoints 4 months after the follow-up visits exclusively for safety reasons and without disclosure of the randomization. Additionally, ADEs will be monitored regularly. The results will be available only to the SDMC. The SDMC will report any recommendation on necessary trial modifications or a trial abort to the principal investigator and the coordinating monitors. The SDMC will recommend termination of the trial if clinically relevant safety concerns arise in either the control or the intervention group. No explicit stopping rules have been developed.

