### Data management and sample size calculation

Sample size calculation is based on binary analysis of the primary endpoint (non-elective hospital admission or death within 2 years). The study sets out to prove superiority regarding the primary endpoint. Garfinkel observed an 18 % absolute risk reduction achieved by prudent reduction of polypharmacy in a non-randomized controlled trial (from 30 % in the control group to 12 % in the intervention group regarding the annual referral rate to acute care facilities) [23]. This corresponds to a relative risk reduction of 60 % regarding this endpoint.

However, considerably smaller reductions than this still represent substantial clinical and economic benefits; therefore, this study is powered to detect a relative risk reduction of 20 %. We expect to recruit healthier patients than Garfinkel and will use non-elective hospital admission (yes/no) instead of referral rate, because it seems less susceptible to bias. In addition, our primary outcome will combine mortality with hospital admission, since there may be trade-off between these. We have been unable to find empirical data on which to estimate the rate of admission and mortality for our population, but in England in 2010 there was an average of approximately one completed consultant episode for every person in the population aged 75 years or older [43]. The primary outcome of dropouts is coded as an ‘event’ in both groups. Therefore, we consider a low estimate to be half the rate observed by Garfinkel [23]: an annual admission and mortality rate of 15 % of control patients; or 30 % in 2 years. Calculations show that in the event of the actual rate being higher than this, the sample size given below is conservative (ie., larger, rather than smaller, than requirement).

A relative risk reduction of 20 % in the intervention group implies a 2-year event rate of 24 % for that group.

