### Limitations of the study

We have explicitly decided to not include any recommendations in the PRIMA-eDS tool for starting patients on additional drugs, and this may be considered a weakness of our study. Our main objective is to demonstrate that the discontinuation of inappropriate drugs can improve patient outcomes. A combined intervention to stop inappropriate and start other (more appropriate) medications would impede us from differentiating out the effect of drug discontinuation.

Furthermore, access to medical records differs by country. Italy and the UK are characterized by a primary care centred health care system, with all medication data and diagnoses available to the GP. In these two countries we expect data from the electronic health records of the GPs to be largely complete. This is not the case in Germany or Austria where patients have direct access to specialists, and not all medication prescribed by a specialist will be known to the GP. We are asking GPs to address medication prescribed by specialists at the study visits to assure completeness of data. Nonetheless, patientsʼ data in these countries carry a risk of being incomplete which might be considered a limitation of our study. However, the problem of incomplete medication data equally affects the intervention and the control group. We therefore believe that due to randomization being stratified by study centre, incomplete medication data will not bias our study results.

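### The unblinded treating GP records the admission part of the primary endpoint, and the article names neither a source outside the practice nor an allocation-blind classification of 'non-elective'

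*Protocol article*

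**What the plan says.** All places are in the protocol article.

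- **Primary outcome:** "The primary outcome is a composite endpoint of first non-elective hospital admission or death during the observation period measured as a binary outcome". On who records it: "Primary outcome measures are recorded by the GPs when they occur or at follow-up visits every 8 months".
- **Blinding:** "Inherent to the study protocol GPs and patients cannot be blinded". The one safeguard given there is "The analyst will be kept blind to GP practice allocation".
- **Monitoring:** for T3 the text says that "monitors will check all reported and not reported non-elective hospital admissions as well as adherence to protocol visits with the practice record". The same check is made by phone at T1 and T2, and the party called is not stated. From T1 to T3, in a random 10 % of practices, "they will check the reported hospital admissions and deaths of all patients of the practice". The monitors are independent, and a monitoring charter is cited but not shown.
- **Data management and sample size calculation:** the investigators "will use non-elective hospital admission (yes/no) instead of referral rate, because it seems less susceptible to bias". Dropouts count as events in both arms.
- **Limitations of the study:** in Germany and Austria, "where patients have direct access to specialists, and not all medication prescribed by a specialist will be known to the GP". The section discusses this for medication data only.

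**The concern.** The person who uses the tool, knows the arm and treats the patient is also the person who records whether an admission occurred and, as far as the article shows, whether it was non-elective. The article names no hospital or insurer source and no classification made without knowledge of the arm.

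The safeguards it does name leave a gap. Comparison with the practice record can find an admission that the practice knew of and did not enter. It cannot find a stay that the practice never learned of, and it does not test the non-elective label independently. Analyst blinding acts after the data are captured. Stratifying by centre balances the quality of records at allocation, but it does not stop capture from diverging by arm afterwards. GP conduct does differ by arm after allocation: intervention GPs carry out tool-based medication reviews at each study visit and control GPs do not.

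At stake is the validity of the primary comparison. A difference in capture between arms cannot be told apart from a treatment effect. A shortfall that is equal in both arms would lower the event rate and cost power.

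**Working it through.** **Inputs from the article:** 30 % v 24 % events at 2 years; two-sided α 5 %; power 80 %; intra-cluster correlation 0.01; mean of 11 patients per practice; attrition of 10 % of patients and 10 % of practices; dropouts coded as events; 1771 per arm, 3542 in total.

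**Step 1: reproduce the stated sample size.**

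- Dropout share: 1 − 0.9 × 0.9 = 0.19.
- Control: 0.19 + 0.81 × 0.30 = 0.4330. Intervention: 0.19 + 0.81 × 0.24 = 0.3844.
- The standard two-proportion formula gives 1605 per arm.
- Design effect: 1 + (11 − 1) × 0.01 = 1.10. Then 1605 × 1.10 = 1765.5 per arm, 3531 in total.
- With Poisson variation in cluster size (design effect 1.11), 1605 × 1.11 gives about 1782 per arm, 3563 in total.

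The stated 3542 lies between these totals, and power at 1771 per arm is 80.1 %. The model below is therefore the plan's own.

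**Step 2: no true effect, events missed or relabelled in one arm only.** The article gives no error rate, so the rates are assumptions. Effective size is 1771 / 1.10 = 1610 per arm.

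For a 10 % relative shortfall:

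- Recorded rate among non-dropouts: 0.30 × 0.90 = 0.27. Analysed rate: 0.19 + 0.81 × 0.27 = 0.4087, against 0.4330.
- SE = √[(0.4330 × 0.5670 + 0.4087 × 0.5913) / 1610] = 0.0174.
- z = 0.0243 / 0.0174 = 1.40. The chance of |Z| > 1.96 is about 29 %.

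For a 5 % shortfall: 0.19 + 0.81 × 0.285 = 0.4209, difference 0.0122, z = 0.70, chance about 11 %.

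**Step 3: protect the deaths.** A death can hardly be labelled elective. Let a share s of composite events be deaths (assumption: 20 % or 30 %) and apply the shortfall m to the rest. The recorded rate is 0.30 × [1 − (1 − s) × m]. For s = 20 % and m = 10 % this is 0.30 × 0.92 = 0.276.

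Chance of a significant result with no true effect (nominal 5 %):

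| Relative shortfall in one arm | All events exposed | 20 % deaths | 30 % deaths |
|---|---|---|---|
| 5 % | 10.7 % | 8.6 % | 7.8 % |
| 10 % | 28.7 % | 20.0 % | 16.4 % |
| 20 % | 80.1 % | 61.0 % | 49.9 % |

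**Step 4: the other direction.** With a true 30 % v 24 % and the shortfall in the control arm (all events exposed), power falls from 80 % to 56 % at a 5 % shortfall and to 29 % at 10 %.

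**The case against.** The strongest case on the other side has several parts.

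- **The monitoring is more than a formality.** Independent monitors search for unreported as well as reported admissions, with phone checks at T1 and T2 as well as the T3 check. This reduces simple omission, so it would be wrong to say that the endpoint is verified only on paper at the end. The gap remains for stays unknown to the practice and for the label. It is also not fully clear whether the T3 check covers every practice.
- **Data are recorded at the same time points in both arms.** No passage shows differential capture or gives a rate. This stands: the bias is a possibility of unknown direction.
- **This is a condensed article.** The full protocol, the monitoring charter and the eCRF may hold a definition of non-elective or a source check. That is why the point rests on what the article fixes, namely the unblinded recorder and the practice record, and not on missing detail.
- **Some patients keep event status anyway.** A patient with several admissions loses it only if all of them are missed or relabelled. This pulls the figures down.

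Three stronger readings are tempting but not supported:

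- A reader might take the yes/no wording in the sample size section to mean that the GP ticks a single elective/non-elective box. It describes the outcome variable. The secondary endpoints include number and duration of admissions, and time-to-event and count analyses are planned, so episode-level data are probably collected.
- A reader might infer from the limitations section that GPs in Germany and Austria do not learn of emergency admissions. That section speaks of medication prescribed by specialists and says nothing on hospital stays.
- A reader might remove the dropouts (1771 × 0.81 = 1434 per arm) and obtain z = 0.03 / 0.0177 = 1.70, about 40 % false positives at a 10 % shortfall. The plan keeps dropouts in the analysis as events, and the matching figure is 29 %, or lower once deaths are protected.

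**Conclusion.** The point holds as a weakness in how the admission component is ascertained. It is not evidence that the trial will be biased. If one arm records 5 % fewer events than the other with no true effect, the two-sided error rises from 5 % to about 11 %; at 10 % it rises to about 29 %. With 20 to 30 % of events being deaths, the figures are about 8 to 9 % and 16 to 20 %. A shortfall in the control arm could equally hide a real benefit.

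These figures rest on assumed capture rates and an assumed share of deaths, on 19 % dropouts coded as events in both arms, and on a design effect of 1.10. A 10 % relative shortfall among non-dropouts is 3 points (30 % v 27 %), half of the 6-point effect the trial is sized to detect, so a modest imbalance would matter. The article's preference for admission over referral as less open to bias is reasonable, but it does not deal with who classifies the admission.

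**What to change.** In both arms:

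1. Record facts for every hospital stay: admission and discharge dates, admission route, and whether and when the stay was booked in advance. Support the entry with the discharge letter where the practice holds it.
2. Derive 'non-elective' from these facts by one prespecified rule, applied at the data centre without the allocation.
3. At the existing 8-, 16- and 24-month visits, ask every patient or carer one scripted question on hospital stays since the last visit, so that stays unknown to the practice can surface.

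The cost is a few eCRF fields, of which the dates are probably collected already, one question per visit and slightly longer data entry per admission. No extra visit or assessor is needed. The GP still enters the facts and patients are unblinded, so the bias is reduced and not eliminated.

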### Secondary outcome

Secondary endpoints are all cause mortality, non-elective hospital admission (number of episodes and duration), falls (number and severity), fractures, quality of life (SF-12v2), the number and types of drugs (total number, number discontinued, number not discontinued despite the recommendation to discontinue, number re-administered for symptom control), adverse event rate, and medication costs over the observation period.

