## Methods/Design

### Trial design

The PRIMA-eDS trial is a multicentre cluster-randomized controlled trial with an observation time of 2 years using GP practices as clusters of randomization. It will be conducted at five study centres recruiting GP practices in their corresponding region/country. The principal trial centre and coordinator of the study is the Institute of General Practice and Family Medicine of Witten/Herdecke University (Germany). The other four study centres are the University of Manchester (United Kingdom), the Rostock University Medical Centre (Germany), the Paracelsus Medical University (Austria), and the South Tyrolean Academy of General Practice (Italy).

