After entering diagnoses, current medication including drugs that have not been prescribed by the GP, and other patient data (current symptoms, biometric measurements and laboratory values), the GP will receive an on-screen “Comprehensive Medication Review” report, generated by the PRIMA-eDS tool and detailing all the relevant prescribing recommendations. The patient’s list of medications can then be reviewed and revised accordingly by the GP in a shared decision-making process with the patient. A record will be made of which recommendations were adopted. GPs will be explicitly instructed that any decision to continue or discontinue a drug according to or against the advice of the PRIMA-eDS tool remains at the discretion of the GP and the patient. All intervention GPs will be trained to use the PRIMA-eDS tool. Training options will include personal training, group training, webinars and a handbook.

Before the start of the trial, the tool has been evaluated in a feasibility study which has been presented at the 16^th^ annual meeting of the German Network for Evidence-based Medicine [33]. The tool as a whole has not yet been tested for validity or reliability, but substantial work has demonstrated the feasibility and applicability of the various components of the tool. The use of clinical decision support (CDS) for promoting appropriate, safe, and cost-effective drug use has become common as an inbuilt feature of advanced electronic health record (EHR) systems [34]. CDS can also be implemented as an externally offered service that is integrated with an EHR [35]. The EBMeDS CDS system (www.ebmeds.org) is a service developed by Duodecim Medical Publications Ltd. since 2003. An early version of EBMeDS containing a variety of decision support rules was evaluated in a randomized controlled trial [36]. Databases on drug-drug interactions and renal dosing developed by Medbase Ltd. have been included in EBMeDS. The design and usability of these databases have been described [31, 37, 38], and their impact evaluated [39, 40]. Because of its modular design, comprehensiveness and easy integration with EHRs and case-report forms, EBMeDS was selected as the platform for developing the PRIMA-eDS tool. All components of the tool are regularly updated during the trial by the corresponding provider and by the PRIMA-eDS consortium.

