### Documentation and monitoring

#### Baseline-examination

Shortly after consent is obtained, the GPs will assess the following parameters and record all data in each patient’s electronic case report form (eCRF):Age, sex, height, weight, systolic and diastolic blood pressureAll drugs with a systemic effectAll diagnosesCurrent symptoms (within last month)Falls within the last 3 months requiring medical attentionCreatinine, blood glucose, alanine aminotransferase (ALT), hemoglobin A1c (HbA1c), platelet count, international normalized ratio (INR), cholesterol, low-density lipoprotein (LDL)-cholesterol, high-density lipoprotein (HDL)-cholesterol, triglycerides, potassium, sodium. With the exception of creatinine level, GPs should not initiate additional laboratory examinations solely for the study due to ethical reasons and to avoid contamination in this pragmatic trial. They should rather enter the latest values available in the health record and include the date of the measurement. If the tool requires a laboratory value for a recommendation, it provides this information to the GP. The GP can then decide whether to perform the laboratory examination or notSmoking behaviorMedical procedures (e.g., stenting, heart valve replacement)Frailty according to the Clinical Frailty Scale [41]Quality of life questionnaire (SF-12v2) to be filled out by the patient [42]. This will be administered by the GP to the patient on paper. The filled out forms will then be sent to the study centre for electronic data entry

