### Follow-up

At follow-up visits (at 8 and 16 months) and final examination (24 months) the same data will be recorded again for all patients. One exception is the quality of life questionnaire (SF-12v2), which will be collected at 8 and 24 months only. GPs in the intervention group will conduct further medication reviews using the PRIMA-eDS tool for their participating patients, and make the medication changes they think are appropriate, at each follow-up and final visit. Control group GPs will continue to provide usual care to their patients.

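### The falls item looks back 3 months at visits 8 months apart, so the dedicated falls record covers 9 of the 24 months of observation

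*Protocol article*

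**What the plan says.** Under Trial design, the protocol article describes a "multicentre cluster-randomized controlled trial with an observation time of 2 years". Under Secondary outcome, the endpoints include "falls (number and severity), fractures, quality of life (SF-12v2"), that is, both how many falls occurred and how severe they were.

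The data source is the list under Baseline-examination. Its falls item covers falls "within the last 3 months requiring medical" attention. The Follow-up section then says: "At follow-up visits (at 8 and 16 months) and final examination (24 months) the same data will be recorded again for all patients". It names a single departure from that rule: "One exception is the quality of life questionnaire (SF-12v2), which will be collected at 8 and 24 months only". No other look-back for falls is given for the follow-up visits.

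**The concern.** A 3-month look-back is reasonable at baseline, where it describes recent history. Carried over to visits 8 months apart, it leaves the first 5 months of every interval outside the item. Intervention practices review medication at each visit, so those 5 months are also the ones that nominally follow a review.

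Falls matter in a trial of stopping or changing drugs in older patients, both as a possible benefit and as a possible harm. If the item is used as written, the endpoint rests on a minority of follow-up time. The comparison then describes the later part of each interval rather than the 2 years. An analysis plan cannot repair this, because events that were never asked about cannot be recovered by analysis.

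**Working it through.** The plan gives no figure for the falls endpoint to reproduce. Its only calculation, the sample size, concerns the primary outcome and plays no part here.

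**Inputs**
- Observation time: 24 months (Trial design).
- Visits after baseline: 8, 16 and 24 months (Follow-up).
- Look-back of the falls item: 3 months (Baseline-examination), repeated unchanged (Follow-up).

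**Coverage**
- Covered time = visits × look-back = 3 × 3 = 9 months, namely months 5-8, 13-16 and 21-24.
- Covered share = 9 / 24 = 37.5%.
- Uncovered time = 24 − 9 = 15 months (15 / 24 = 62.5%), namely months 0-5, 8-13 and 16-21.
- With a look-back to the previous visit: 3 × 8 = 24 of 24 months.

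**Precision, upper bound.** Assume a constant fall rate and Poisson counts. The variance of the log rate ratio is then inversely proportional to observed time, so the ratio of standard errors is √(24 / 9) = 1.63.

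**Precision with variation between patients.** Let m be the mean number of falls per patient over 24 months and k the overdispersion. The ratio becomes √[(1/(0.375m) + k) / (1/m + k)]. The article gives neither value, so the figures below are assumptions for illustration, with m = 1:

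| k | Calculation | Ratio |
|---|---|---|
| 0 | √(2.667 / 1) | 1.63 |
| 0.5 | √(3.167 / 1.5) | 1.45 |
| 1 | √(3.667 / 2) | 1.35 |

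Correlation within practices would lower the ratio further. The coverage of 37.5% depends on none of these assumptions.

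**Position of the gaps.** Reviews are scheduled at baseline and at 8 and 16 months, and each is followed by 5 uncovered months. The first alignment is only nominal: a practice is randomized once its recruitment is complete, so its first review may come some time after a patient's baseline record.

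**The case against.** **Other channels may catch falls.** GPs report serious adverse events when they learn of them and all adverse events at visits, with no 3-month limit. A fall leading to a non-elective admission is recorded with the primary outcome. This stands in part, and it rules out saying that every fall in the uncovered months is missed. But the article does not say that these reports feed the falls endpoint. The Secondary outcome section lists the adverse event rate separately, and the Monitoring section treats falls as an eCRF entry of its own.

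**An article condenses its protocol.** Follow-up questions may differ in the eCRF, and the sentence about repeating the data may be shorthand. That would excuse a missing detail, such as a severity grade, which is not held against the plan here. It does not excuse the look-back, because the article states the window, its repetition and the sole exception.

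**The 2-year period is inferred for falls.** In "adverse event rate, and medication costs over the observation period", the period attaches most directly to costs. This is fair. A falls count over 2 years is the natural reading in a trial with that observation time, but it is not spelled out. Restating the endpoint would therefore also resolve the mismatch.

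**Both arms share the same window.** This stands. The rate ratio for the sampled months is a valid comparison. Nothing in the documents shows that effects on falls concentrate in the months just after a review.

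**A reader might extend the point to fractures and medication costs.** The documents do not support that. Fractures can enter through the diagnoses recorded at each visit and through adverse-event reports, neither limited to 3 months. For costs, drug lists at 0, 8, 16 and 24 months span the period, and the Intervention section adds: "A record will be made of which recommendations were adopted". No carry-forward rule is stated that could be faulted. How the lists become costs can be left to the full protocol or analysis plan.

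**Conclusion.** The point holds for falls. On the literal text, the dedicated item covers 9 of 24 months, and 62.5% of follow-up lies outside it. The consequence is lost coverage and precision: a standard error up to 1.63 times that with full coverage under a constant rate and pure Poisson counts, and less otherwise. A rate ratio from the covered months represents the full 2 years only if the effect is similar in the uncovered ones.

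A reader might infer that the falls comparison is biased between arms, or that most falls are lost to the trial altogether. Neither is shown: the window is the same in both arms, and other reporting may pick up some events. The point concerns one secondary endpoint and does not touch the primary outcome or the sample size. It is still worth correcting, because the change is cheap and unasked events are hard to recover later.

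**What to change.** At the 8-, 16- and 24-month visits, ask for falls that needed medical attention since the last visit, each with date and severity. Keep the 3-month window for baseline only. Bring Baseline-examination, Follow-up and Secondary outcome into agreement on this.

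The cost is a change of wording plus date and severity fields in the eCRF, where these do not already exist. The downside is longer recall, limited because falls that needed medical attention are usually in the practice record.

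Timing needs care. Recruitment started in January 2015, so the first 8-month visits fall around September 2015. If some visits have already used the 3-month window, the fall dates collected from then on allow a common window, the 3 months before each visit, to be analysed for everyone.

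If the item cannot be changed, restate the endpoint as falls needing medical attention in the 3 months before each visit, and report it as such. That costs nothing in data collection but gives up the claim to a 2-year count.
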